### 17.3.2 Baseline comparability

Participants in each intervention group will be described separately with respect to baseline characteristics such as maternal age, gestational age, number of previous pregnancies, area of residence and anaemia on recruitment. The clinical importance of any imbalance will be noted and taken into account in further analyses.

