## 17 Statistical methods

### 17.1 Sample size

The trial will use a stratified design with one strata for primigravidae and secundigravidae and one strata for multigravidae. It is designed to detect a 25% reduction (RR 0.75) in composite adverse birth outcomes (SGA, low birth weight and pre-term birth) in women in their first and second pregnancies with an 90% power and a 2-sided significance level of 0.05, if the rate of placental malaria in the IPT-SP group is similar to that found ongoing observational studies of women receiving routine care in the same area of Malawi. The proposed difference is based on four previous trials of IPTp which jointly reduced low birth weight by 29%. Thus the efficacy of ISTp is expected to be similar to the efficacy of IPTp before the emergence of widespread SP resistance. In the ongoing IPT-mon study in Malawi, the incidence of SGA, low birth weight or preterm birth was 40.3% (N=494) ([name], personal communication). Therefore the study is designed to detect a 25% difference between 40.3% in the control (IPTp) group and 30.2% in the intervention (ISTp) group.

This would require 491 participants in each arm or 982 in total. To allow for a 15% loss to follow-up, 1155 women in their first and second pregnancies will be recruited. This sample size would also have an 81% power to detect a 25% or greater reduction in placental malaria (active or past infection), with a significance level of 0.05. If a power of 80% is used, the study can detect a difference of 21.8% or greater in the primary endpoint. If the incidence is 33.3% instead of 40.3% the study still has 80% power (instead of 90%) to detect a 25% reduction.

The trial is also designed to detect a 50% reduction in past or present placental malaria infection at delivery in multigravidae, based on previous studies of IPTp, assessed by placental histopathology and RDT. The current rate in women in Malawi who are taking IPTp-SP is estimated from IPT-mon at 20.5% ([name], personal communication). A reduction by 50% to 10.25% will require 213 women per arm or 426 in total. To allow for a 15% loss to follow-up we will recruit 500 multigravidae.

The total sample size will therefore be  $1155 + 500 = 1655$ .

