## 17.2 Randomization

Two randomization sequences will be computer-generated by the study statistician at Liverpool School of Tropical Medicine, one for women in their first and second pregnancies and another for multigravidae. The method used for each will be block randomization, stratified by study site to ensure an equal proportion of participants in each intervention group from each site. The length of each block will vary and will ensure that allocation concealment is fully maintained and allocation well distributed over the seasons. The allocation ratio for the two study arms will be 1:1.

Recruitment will be 'competitive' between study sites, meaning that the number of participants recruited at each site may differ depending on the respective rates of enrolment. A sufficient number of randomization codes will be generated for each site to allow for this.

The randomization sequences will be sent to the study sites in Malawi and local investigators will prepare opaque envelopes, numbered sequentially, with the allocated group code and details for that number inside. For each newly enrolled participant, an envelope from the correct sequence (according to gravidity group) will be opened sequentially to identify the group that they are allocated to, thus concealing the upcoming allocation from the participants, clinic staff and study staff. The number on the envelope represents the study number allocated to that participant and will become their unique identifier in the trial. This number will be recorded with their screening registration number on their CRF, and the participants provided with a trial identity card confirming their study number. Once a study number has been assigned to a participant it will not be used again, for example if a participant discontinues. If a study number is allocated incorrectly, it will not be reassigned and randomization will continue with the next sequential number.

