### 17.3.3 Efficacy

The primary efficacy analysis will be the assessment of the superiority of ISTp-DP over IPTp-SP in women in their first and second pregnancies for the prevention of any of the following: SGA, pre-term birth or low birth weight. Similar analyses will be undertaken for the additional primary outcome of evidence of active or recent infection assessed at delivery by placental histopathology and RDT in women in their third to fifth pregnancies, and for the secondary efficacy outcomes. Impact will be determined by gravidity strata as the primary analysis. As a secondary analysis we will also estimate the overall estimated effect, extrapolated to all gravidity groups using a weighted analysis providing extra weight to the observations in multigravidae so that the final estimate represents the distribution of gravidity groups in the population attending antenatal clinics (based on antenatal clinic records).

Generalised linear models will be used where appropriate to assess the effect of the intervention according to different characteristics of the participants. Treatment effects will be expressed in terms of relative risk and risk difference for dichotomous variables and mean difference for continuous variables, and the corresponding 95% confidence intervals. Superiority will be defined as a positive treatment effect that is greater in the ISTp group than the IPTp group, where the 95% confidence interval does not include the point of no difference (RR value of 1).

Both modified intention-to-treat and per-protocol analyses will be undertaken for the efficacy analyses. The modified intention to treat analysis will be the primary analysis to assess superiority. In the absence of evidence for superiority, the prospectively defined non-inferiority margin will be 15% for adverse outcome or placental malaria in the intention to treat and per protocol populations (relative difference between endpoints of 15% (i.e. RR 0.85); e.g. 24.5% versus 28.8% for adverse birth outcome).

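### Site stratifies the randomisation, but the primary analysis specifies no site term, and the only covariate rule is a judgement of imbalance made after the fact

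*Combined protocol and SAP*

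**What the plan says.** - **Randomisation (section 17.2).** There is one sequence per gravidity group, each using "block randomization, stratified by study site to ensure an equal proportion of participants in each intervention group from each site".
- **Primary analysis (section 17.3.3).** The effect is estimated within each gravidity group, so that stratification factor is respected. Results are a relative risk and a risk difference, and superiority is declared when the 95% confidence interval for the relative risk excludes 1. The only sentence on models is: "Generalised linear models will be used where appropriate to assess the effect of the intervention according to different characteristics of the participants". No link function, site term, stratified test or covariate list is given.
- **Baseline comparability (section 17.3.2).** The arms are described on characteristics that include number of previous pregnancies and area of residence. Then: "The clinical importance of any imbalance will be noted and taken into account in further analyses".
- **Site elsewhere.** Section 6.2.3 lists location as an exploratory effect modifier. The synopsis gives two sites. Section 7.1 gives three or more, names four, and allows clinics in neighbouring districts to be added.

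**The concern.** Blocking by site makes the arms more alike than simple randomisation would. An analysis without site does not credit that balance, so its standard error is too large wherever risk differs between sites. Site is fixed by design and known for every woman, so leaving it unspecified has no benefit.

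The covariate rule is the more important gap. It depends on a judgement of clinical importance made once the data are visible, in an open-label trial where one confidence interval decides success. Chance imbalance is also a weak reason to adjust. What brings precision is how strongly a baseline predicts the outcome, and that can be settled beforehand. The half-way interim analysis (section 17.4) needs a defined test statistic too, and the non-inferiority fallback in section 17.3.3 would inherit the same open choice.

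**Working it through.** **1. The plan's own figures.** Inputs from section 17.1: "25% difference between 40.3% in the control (IPTp) group and 30.2% in the intervention (ISTp) group", "with an 90% power and a 2-sided significance level of 0.05". A relative risk of 0.75 gives 0.75 × 0.403 = 0.30225, so the difference is d = 0.10075 and the mean risk is p̄ = 0.352625.

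n = [1.960·√(2p̄(1−p̄)) + 1.282·√(p₁(1−p₁) + p₂(1−p₂))]² / d² = 470.5 per arm.

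With the continuity correction, (n/4)·[1 + √(1 + 4/(n·d))]² = 490.2, so 491. This matches "This would require 491 participants in each arm or 982 in total". Then 982/0.85 = 1155.3, matching the 1155 to be recruited. For multigravidae, 20.5% against 10.25% at 80% power gives 193.2, and 213 after correction, matching "A reduction by 50% to 10.25% will require 213 women per arm or 426 in total". None of these calculations contains a site term.

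**2. What leaving site out costs.** The documents give no site-specific risks, so the spread is an assumption: four equal sites, mean control risk 40.3%, 491 first and second pregnancies per arm, balanced within site. An unstratified two-proportion test was compared with a site-stratified Cochran-Mantel-Haenszel test in 40,000 simulated trials per row. The Monte Carlo error at 5% is √(0.05 × 0.95/40,000), about 0.1 point. The variance ratio, with qₛ = 0.75pₛ, is

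[mean pₛ(1−pₛ) + mean qₛ(1−qₛ)] / [p̄(1−p̄) + q̄(1−q̄)], where p̄ and q̄ are now the arm means.

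At ±10 points it is 0.4428/0.4515 = 0.981, and 491 × 0.981 is about 482.

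| Assumed spread | Site risks | Power, without / with site | Type I error, without / with site | Variance ratio | Equivalent n per arm |
|---|---|---|---|---|---|
| 0 | 40.3% | 91.4 / 91.3% | 4.9 / 4.9% | 1.000 | 491 |
| ±5 | 35.3-45.3% | 91.1 / 91.1% | 5.0 / 5.1% | 0.995 | 489 |
| ±10 | 30.3-50.3% | 91.3 / 91.6% | 4.7 / 5.1% | 0.981 | 482 |
| ±15 | 25.3-55.3% | 91.8 / 92.5% | 4.3 / 4.9% | 0.957 | 470 |
| ±20 | 20.3-60.3% | 92.1 / 93.1% | 3.9 / 5.0% | 0.923 | 453 |

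Power starts above 90% because 491 carries a continuity correction that the simulated tests do not.

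**3. Cross-check.** The share of outcome variance due to site is Var(pₛ)/[p̄(1−p̄)]. Assumed site risks of 33, 38, 42 and 48% give 0.00302/0.2405 = 1.3%. Risks of 28, 36, 44 and 53% give 0.00862/0.2405 = 3.6%. Power is then Φ[(1.960 + 1.282)/√(1−R²) − 1.960], which moves 90% to 90.4% and 91.0%. If site and baseline covariates together explained 5-10% of the variance, the same formula gives 91.4-92.7%, and 82.0-84.0% from a starting 80%. The documents support no value of R².

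**4. What open model choice can do.** This is an illustrative null simulation with assumed inputs: 982 women, five independent covariates with log-odds 0.2 or 0.4 per SD, 4,000 replicates (Monte Carlo error about 0.3 point).

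| Strategy | Type I error |
|---|---|
| One prespecified model with all five covariates | 4.7-5.1% |
| Adjust only for covariates imbalanced at p < 0.10 | 4.3-4.6% |
| Most favourable of seven models (unadjusted, each covariate singly, all five) | 6.8-8.2% |

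The inflation comes from free choice between models. A fixed imbalance rule does not produce it, but section 17.3.2 is not a fixed rule.

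**5. Room for a model in multigravidae.** Expected events at the design rates are 213 × 0.205 + 213 × 0.1025 = 43.7 + 21.8, about 65. A log-binomial model with site, gravidity and baseline infection may fail to converge on that number.

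**The case against.** The strongest reply is that this is silence, and a mild one. A reader might infer that the plan ignores site, or that the primary estimate is adjusted only for imbalances found later. The documents support neither reading: section 17.3.3 does not exclude a site term, and the further analyses of section 17.3.2 may well be supportive ones. An unadjusted comparison within gravidity group, if fixed in advance, is valid. Its error rate is at or below nominal, so a superiority claim is not endangered.

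A reader might also infer a real loss of power, or a gain worth 5-10% more women. The first is at most about one point under the widest spread tried. The second needs an R² that the documents do not give and that has not been derived for any particular covariate set. A third tempting inference, that adjusting for imbalance in itself inflates type I error, is contradicted by step 4.

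All of this stands. It limits the size of the point but does not remove it. The text still does not say which model yields the deciding interval, and the sentence in section 17.3.2 sits immediately before the efficacy section with nothing to keep it out of the primary analysis.

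**Conclusion.** The point holds as a gap in specification with a small precision cost. Site is a randomisation stratum with no stated place in the primary analysis, and the only covariate rule is a judgement after the fact of unstated scope. Omitting site costs 0-8% of efficiency and 0-1 power point, with type I error of 3.9-5.0%. These figures rest on assumed spreads of 0 to ±20 points over four equal sites and cover first and second pregnancies only. Any power gain beyond about one point rests on an assumed R².

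The larger stake is that the primary relative risk can depend on the model chosen. The 6.8-8.2% is an illustration of what unrestricted choice permits under assumed covariates. It is not an estimate of this trial's error rate. The sample sizes need no change.

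**What to change.** Amend the analysis section before any comparative data are seen, which means before the interim analysis:

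1. State that the primary relative risk and risk difference in each gravidity stratum come from one prespecified site-adjusted model. An example is modified Poisson with robust standard errors, plus its identity-link counterpart for the risk difference. Modified Poisson is a safer choice than log-binomial with about 65 events in multigravidae.
2. Include arm, site, gravidity (first or second; third, fourth or fifth) and baseline malaria infection, regardless of observed imbalance. Take baseline infection from the enrolment microscopy or PCR, which is planned in both arms, and not from the screening RDT, which belongs to one arm.
3. Give a pooling rule for small or late-added sites, and reconcile the number of sites between the synopsis and section 7.1.
4. State a rule for missing baseline results, since the sample depends on consent (section 7.2.7). That section also withholds these results until the end of the trial, so say which statistic the interim analysis uses.
5. Report the unadjusted estimate as a sensitivity analysis. Keep the sentence in section 17.3.2, but confine it to labelled sensitivity analyses.

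The cost is a few sentences and a few lines of code. The variables are already planned for collection, and recruitment is unaffected.

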### 17.3.3 Efficacy

The primary efficacy analysis will be the assessment of the superiority of ISTp-DP over IPTp-SP in women in their first and second pregnancies for the prevention of any of the following: SGA, pre-term birth or low birth weight. Similar analyses will be undertaken for the additional primary outcome of evidence of active or recent infection assessed at delivery by placental histopathology and RDT in women in their third to fifth pregnancies, and for the secondary efficacy outcomes. Impact will be determined by gravidity strata as the primary analysis. As a secondary analysis we will also estimate the overall estimated effect, extrapolated to all gravidity groups using a weighted analysis providing extra weight to the observations in multigravidae so that the final estimate represents the distribution of gravidity groups in the population attending antenatal clinics (based on antenatal clinic records).

Generalised linear models will be used where appropriate to assess the effect of the intervention according to different characteristics of the participants. Treatment effects will be expressed in terms of relative risk and risk difference for dichotomous variables and mean difference for continuous variables, and the corresponding 95% confidence intervals. Superiority will be defined as a positive treatment effect that is greater in the ISTp group than the IPTp group, where the 95% confidence interval does not include the point of no difference (RR value of 1).

Both modified intention-to-treat and per-protocol analyses will be undertaken for the efficacy analyses. The modified intention to treat analysis will be the primary analysis to assess superiority. In the absence of evidence for superiority, the prospectively defined non-inferiority margin will be 15% for adverse outcome or placental malaria in the intention to treat and per protocol populations (relative difference between endpoints of 15% (i.e. RR 0.85); e.g. 24.5% versus 28.8% for adverse birth outcome).

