### 9.2 Secondary outcomes

#### 9.2.1 Secondary efficacy outcomes

1. Placental malaria (any species):
  - a. Past infection detected by histopathology
  - b. Active infection detected by:
    - i. Histopathology
    - ii. Microscopy
    - iii. Rapid diagnostic test
    - iv. Polymerase chain reaction (PCR)
2. Maternal malaria infection (peripheral blood) at delivery, detected by:
  - a. Microscopy
  - b. RDT
  - c. PCR
3. Peripheral malaria infection during pregnancy detected by:
  - a. Microscopy
  - b. PCR
4. Birth weight
  - a. Mean birth weight (grams)
  - b. Low birth weight (<2,500 grams)
5. Gestational age
  - a. Mean gestational age at birth (grams)
  - b. Pre-term birth (<37 weeks)
6. Small for gestational age
7. Maternal haemoglobin and anaemia:
  - a. At delivery
    - i. Mean maternal haemoglobin (g/dL)
    - ii. Anaemia (Hb ≤ 11 g/dL)
    - iii. Moderate to severe anaemia (Hb ≤ 8g/dL)

- b. During third trimester
    - i. Mean maternal haemoglobin (g/dL)
    - ii. Anaemia ( $Hb \leq 11$  g/dL)
    - iii. Moderate to severe anaemia ( $Hb \leq 8$ g/dL)
- 8. Miscarriage (loss of foetus before 28 weeks gestation)
- 9. Stillbirth (birth at 28 weeks or later showing no signs of life)
- 10. Composite endpoint of the primary endpoint plus fetal loss (miscarriage or stillbirths)
- 11. Infant death
  - a. Perinatal death (stillbirth or death within 7 days of birth)
  - b. Neonatal death (death within 28 days of birth)
- 12. Malaria infection of the newborn, detected by analysis of umbilical cord blood with:
  - a. RDT
  - b. Microscopy
  - c. PCR
- 13. Foetal haemoglobin and anaemia by sampling of umbilical cord blood at birth:
  - a. Mean foetal haemoglobin (g/dL)
  - b. Foetal anaemia ( $Hb \leq 12.5$  g/dL)
  - c. Moderate to severe foetal anaemia
- 14. Incidence of documented clinical malaria episodes during the second and third trimesters of pregnancy (history of fever in last 24 hours and documented malaria microscopy or RDT positive)
- 15. Presence of any evidence of malaria infection at term (last antenatal visit), identified through microscopy or PCR, or at delivery, identified through peripheral and placental RDT, microscopy or PCR, or placental histopathology (active or past infection).
- 16. Incidence of other illness episodes apparent at scheduled antenatal clinic visits or resulting in unscheduled clinic visits
- 17. Incidence and prevalence of clinical malaria in infants by seven days and six to eight weeks determined by:
  - a. RDT

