#### 16.1.1 Enrolment

After informed consent has been signed, participants will be randomly allocated (see section 17.2) to receive either IPTp or ISTp (see section 15.1) and issued with a trial identity card with their unique study identification number. Participants will be informed of study intervention they have been allocated to.

At this stage study staff will ask the participant for a home or mobile telephone number if they have one, and home address or a description of the location of their home, and for their verbal consent to be visited at home two days after receiving the study drugs (if they receive DHA-PQ) and whenever they do not attend scheduled appointments.

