#### 16.1.2 Baseline assessment

A baseline assessment will be conducted for each participant comprising demographic information, socioeconomic information, insecticide treated net (ITN) and indoor residual spraying use, medical and obstetric history, and clinical assessment. Any relevant information already collected during the screening process or at previous antenatal appointments for the same pregnancy will be copied from the antenatal cards onto the CRF, so that questions, tests and examinations are not unnecessarily duplicated.

Study-relevant information recorded at the first visit will include age; area of residence; prior use of ITNs; number of previous known pregnancies and number of previous births. Clinical assessment will include height and weight, fundal height, reported date of last menstrual period and estimated gestation.

A 5 ml venous blood sample will be taken and used for both routine and study-specific testing. This will be obtained after consent for eligibility screening has been obtained but before consent for enrolment in the trial; women who have not been tested for HIV in their current pregnancy will be tested for HIV, and all women will be tested for anaemia and haemoglobin levels. Women not previously tested for syphilis in this pregnancy will be tested and treated if positive. The same blood sample will be prepared for later study-specific testing for malaria (blood smear microscopy and PCR), for markers of immunity to *P. falciparum* malaria, and for markers of iron deficiency. Aliquots of separated blood plasma will be stored at -20 or -80C for immunity studies. A filter-paper sample will be prepared and stored for future research if the woman has given her consent for this.

If not already done, an ultrasound scan will be done at this visit or at a separate visit within a month of enrolment.

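### Mean maternal haemoglobin in the third trimester and at delivery has no prespecified adjustment for booking haemoglobin, so precision on these two secondary outcomes is given up

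*Combined protocol and SAP*

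**What the plan says.** - **Outcomes.** Section 9.2.1, item 7, lists mean maternal haemoglobin at delivery and in the third trimester, with two grades of anaemia at each time. That makes six outcomes, two of them means. All are secondary.
- **Booking value.** Section 16.1.2 says "all women will be tested for anaemia and haemoglobin levels". The sample is "obtained after consent for eligibility screening has been obtained but before consent for enrolment in the trial". Section 16.1.1 then states: "After informed consent has been signed, participants will be randomly allocated". So booking haemoglobin precedes allocation. Section 10 also uses it to decide eligibility.
- **Later values.** Section 16.4.2 tests all women at the final antenatal visit, and section 16.8.1 tests the mother at delivery.
- **Analysis.** Section 17.3.3 states: "Treatment effects will be expressed in terms of relative risk and risk difference for dichotomous variables and mean difference for continuous variables", with 95% confidence intervals. It names no covariate. Its one reference to regression is: "Generalised linear models will be used where appropriate to assess the effect of the intervention according to different characteristics of the participants".
- **Baseline differences.** Section 17.3.2 lists anaemia on recruitment among the characteristics to be described and adds: "The clinical importance of any imbalance will be noted and taken into account in further analyses".

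**The concern.** When an outcome has also been measured before randomisation, the baseline value usually explains part of the spread in the later value. A linear model that includes it estimates the same treatment difference with a smaller standard error. Here the baseline value is collected on every woman in any case, yet the plan does not say that it will be used.

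The two provisions that might supply the adjustment do not secure it. The regression sentence in section 17.3.3 reads as a look at how the effect varies between kinds of women, not as baseline adjustment. Section 17.3.2 acts only once an imbalance has been noticed, and gives no threshold, variable list or model. If the arms happen to be balanced, nothing is triggered and the precision is lost. If they are not, the choice to adjust is made after the data are seen, in an open-label trial (section 7.2.3). At stake is the width of the interval on mean haemoglobin, and whether its analysis is fixed in advance.

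**Working it through.** **Inputs from section 17.1.** The documents state no sample size, power or standard deviation for haemoglobin, so there is no haemoglobin figure to reproduce. The evaluable numbers for the primary outcomes serve as a guide: 491 per arm in first and second pregnancies and 213 per arm in multigravidae. Both can be recovered with the continuity-corrected formula for two proportions:

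- 40.3% v 30.225% (that is, 0.75 × 40.3%), two-sided 0.05, 90% power: 491 per arm, 982 in total; 982 / 0.85 = 1155.3, against 1155 planned.
- 20.5% v 10.25%: 213 per arm if 80% power is assumed, since the section states no power for this stratum; 426 / 0.85 = 501.2, against 500 planned.

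**Assumed input.** ρ is the correlation, within arm and gravidity stratum, between booking and later haemoglobin. The documents do not give it, so it is varied from 0.2 to 0.6.

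**Formulas** (large sample, equal arms of n, outcome standard deviation σ)

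- Variance of the unadjusted mean difference: 2σ²/n.
- Variance after adjustment for booking haemoglobin: (2σ²/n)(1 − ρ²).
- Ratio of interval widths, adjusted to unadjusted: √(1 − ρ²).
- Unadjusted sample giving the same precision: n / (1 − ρ²).
- Difference detectable with 80% power, in units of σ: (1.960 + 0.842) × √(2/n) × √(1 − ρ²).
- Power for an effect that has 80% power unadjusted: Φ(2.802/√(1 − ρ²) − 1.960).

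Without adjustment, the detectable difference is 2.802 × √(2/491) = 0.179σ in first and second pregnancies, and 2.802 × √(2/213) = 0.271σ in multigravidae.

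| Assumed ρ | 1 − ρ² | Interval width ratio | 80% power becomes | Equivalent n per arm (491) | Detectable difference, G1–2 | Detectable difference, G3+ |
|---|---|---|---|---|---|---|
| 0.2 | 0.96 | 0.980 | 82% | 511 | 0.175σ | 0.266σ |
| 0.3 | 0.91 | 0.954 | 84% | 540 | 0.171σ | 0.259σ |
| 0.4 | 0.84 | 0.917 | 86% | 585 | 0.164σ | 0.249σ |
| 0.5 | 0.75 | 0.866 | 90% | 655 | 0.155σ | 0.235σ |
| 0.6 | 0.64 | 0.800 | 94% | 767 | 0.143σ | 0.217σ |

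The narrowing of the interval depends on ρ alone. The detectable differences also depend on how many women have a haemoglobin result, which may differ from 491 and 213.

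**The case against.** The strongest reply is that the plan does not commit to an unadjusted comparison. A mean difference is an effect measure, and an adjusted linear model reports one too. That is correct. A reader might infer from section 17.3.3 that raw means will be compared, but the text says neither raw nor unadjusted. What can be said is that no adjustment is prespecified. An unadjusted comparison remains the natural default reading, since section 17.3.5 does name covariates for the antibody models and section 17.3.3 names none.

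A second reply is that section 17.3.2 already deals with chance imbalance, and that such imbalance is not bias because the unadjusted interval allows for it. This also stands as far as validity goes. A reader might infer that the haemoglobin estimates would be biased; under randomisation they are not. But an adjustment triggered by imbalance does not deliver the precision gain.

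A third reply is that the correlation may be modest. Women with haemoglobin of 7 g/dL or below are excluded, anaemia found at booking is treated, all participants are given iron and folic acid, and booking at 16 to 28 weeks is followed by measurements at 34 to 37 weeks and at delivery. This is fair, and is why the range starts at 0.2, where the interval narrows by only 2%.

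Three further readings go beyond the documents. They do not rank haemoglobin as the leading maternal outcome; it is one of 19 unranked secondary efficacy items. The factor 1 − ρ² applies to a linear model for a continuous outcome and does not measure any gain for the four anaemia outcomes. And no figure supports a stated gain from adjusting mean birth weight for maternal height, weight or gravidity, while the main gravidity split is already built into the randomisation and the analysis.

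**Conclusion.** The point holds as a missed improvement in efficiency, not as an error that threatens a conclusion. Booking haemoglobin is planned for every woman before allocation, and the plan does not prespecify its use for mean haemoglobin in the third trimester or at delivery. Type I error is also unaffected.

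The size cannot be fixed from the documents. Across assumed correlations of 0.2 to 0.6, the saving is 4% to 36% of the variance, worth about 4% to 56% more women in an unadjusted analysis (1/0.96 = 1.04; 1/0.64 = 1.56). These figures are illustrative, and they assume a roughly linear relation and a booking value for nearly every woman. The gain would be most useful in multigravidae, where the detectable difference is larger.

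**What to change.** Add to section 17.3.3 that mean third-trimester and mean delivery haemoglobin will each be analysed within gravidity stratum by a linear model with treatment, continuous booking haemoglobin and study site as prespecified covariates. Site belongs in the model because section 17.2 stratifies the randomisation by it. The adjusted mean difference with its 95% confidence interval is the reported effect, and the unadjusted means by arm stay as descriptive.

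Also state how a missing booking value will be handled, since section 17.3.7 gives no method. Few should be missing, because the test decides eligibility.

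The same covariate may be named for the anaemia models, without claiming a particular gain. Adjusting mean birth weight for recorded maternal characteristics is optional. Any such choice should be written down before outcomes are examined by arm.

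The cost is a few sentences of analysis text. No visit, sample or extra participant is needed.
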